#### Secondary outcome

##### Bristol rating scale assessment

Used to assess stool properties under visual observation during bowel preparation. 1 point: scattered hard masses, resembling nuts; 2 points: similar to salami but lumpy; 3 points: similar to salami but with superficial cracks; 4 points: similar to salami or snake, smooth and supple; 5 points: supple masses, with clear edges; 6 points: fluffy material, with indistinct edges, paste-like stool; 7 points: watery, without solids.

##### IBS Quality of Life Questionnaire (IBS-QOL scale)

The total score of the scale and the score of each dimension of the scale were calculated separately. The scale consists of 8 dimensions: poor mood, behavioral disorders, self-image, health concerns, avoidance of food, social functioning, sexual behavior and expansion of relationships. The total scale score and each dimension score were converted into standard scores according to the following formula. Standard score = (actual score sum of each item - theoretical minimum score/theoretical score range) ×100%.

##### Evaluation of the evidence efficacy

In accordance with the Guiding Principles for Clinical Research on New Chinese Medicines (Trial), the efficacy index was calculated using the nimodipine method: efficacy index = [(pretreatment score - posttreatment score)/pretreatment score] × 100%, divided into four levels: clinically cured, effective, and ineffective. (1) Clinically cured: disappearance or almost disappearance of major symptoms and signs, effectiveness ≥ 95%; (2) effective: a significant improvement in the main symptoms and signs, 70% ≤ effectiveness < 95%; (3) a significant improvement in the main symptoms and signs, 30% ≤ effectiveness < 70%; (4) ineffective: no significant improvement in the main symptoms and signs, 30% ≤ effectiveness < 95%;

Follow-up observation: (1) Follow-up and observation of all healed and effective cases; (2) Follow-up and re-evaluation every 3 months for a total of 2 times; (3) Follow-up can be done by telephone or letting the patient come to the hospital for re-evaluation or visiting the hospital if necessary; (4) Symptom re-evaluation with a score ≥ 1 level is determined as a relapse, and the follow-up will be stopped next time.

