#### Statistical methods

##### Sample size

The test group sample size (massage with the probiotics group) and the control group (probiotics group) were randomly grouped in a 1:1 ratio, and the sample size was determined according to the bilateral hypothesis test, setting the test criterion as a = 0.05 (bilateral) and test efficacy as β = 0.20. The efficiency of the test group in the preexperimental observation is 90, and the efficiency of the control group is 60. The required sample was calculated to be approximately 60 cases, with an increase of 10% of cases taken off, and the actual sample size is approximately 66 cases; that is, 33 cases in the test group and 33 cases in the control group are selected.

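### The efficacy grades of a secondary outcome overlap and leave a gap: ineffective is printed as 30% to below 95%, so no grade covers an index below 30%

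*Protocol article*

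**What the plan says.** All places are in the Protocol article.

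- **Evaluation of the evidence efficacy** (a secondary outcome) defines the index as "efficacy index = [(pretreatment score - posttreatment score)/pretreatment score] × 100" per cent and says that it is "divided into four levels: clinically cured, effective, and ineffective". Four bands follow:
  1. Clinically cured: "disappearance or almost disappearance of major symptoms and signs, effectiveness ≥ 95" per cent.
  2. "effective: a significant improvement in the main symptoms and signs, 70% ≤ effectiveness < 95" per cent.
  3. A band with no name: "3) a significant improvement in the main symptoms and signs, 30% ≤ effectiveness < 70" per cent.
  4. "ineffective: no significant improvement in the main symptoms and signs, 30" per cent to below 95%.
- The same section then limits follow-up to the healed and effective cases.
- **Statistical analysis** assigns chi-square tests to the efficacy grading.
- **Sample size** plans on response rates: "The efficiency of the test group in the preexperimental observation is 90, and the efficiency of the control group is 60". It does not say where these rates come from in terms of the grades.
- **Abstract, Methods/design** describes follow-up observations in both groups and does not restrict them by grade.

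**The concern.** A graded outcome needs categories that do not overlap and that together cover every possible value. The printed bands do neither. The fourth band repeats the second and third, and nothing covers a small improvement, no change or a worsening. The wording adds to the conflict: grade 3 claims a significant improvement, in the same terms as grade 2, while grade 4, which covers the same index values, denies one.

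Two uses of the grades depend on this. The chi-square test needs each patient in exactly one cell. The follow-up selection needs to know who is effective, yet a patient between 70% and 95% is inside that set under grade 2 and outside it under grade 4, and the standing of the unnamed grade 3 is unclear. If the bounds are settled only once results are known, the choice of grading could follow the data.

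**Working it through.** **Inputs** (Evaluation of the evidence efficacy): index = (pre − post)/pre × 100%; grade 1 is ≥ 95; grade 2 is 70 to < 95; grade 3 is 30 to < 70; grade 4 is 30 to < 95.

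**Step 1. Apply the four bands literally.**

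| Index (%) | Grades received |
|---|---|
| below 30 (for example −10, 0, 20, 29.9) | none |
| 30 to < 70 (for example 50) | 3 and 4 |
| 70 to < 95 (for example 80) | 2 and 4 |
| 95 and above | 1 only |

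The union of grades 2 and 3 is [70, 95) ∪ [30, 70) = [30, 95), which is exactly the printed grade 4.

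**Step 2. Count over the whole-number values 0 to 100.**

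- No grade: 0 to 29, 30 values.
- Two grades: 30 to 94, 65 values.
- One grade: 95 to 100, 6 values.
- Check: 30 + 65 + 6 = 101.

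These are counts of index values, not of patients. All negative values also have no grade.

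**Step 3. Apply the bands with grade 4 read as < 30.** The bands become ≥ 95, 70 to < 95, 30 to < 70 and < 30. Every value, negative ones included, receives exactly one grade. No other single range for grade 4 does this, because the other three leave only < 30 free.

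**Step 4. Check the sample size, to see whether it is affected.** Inputs from Sample size: rates 90 and 60 (read as percentages, since no unit is given), two-sided 0.05, power 80%, 1:1 allocation, 10% allowance.

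- Arcsine formula: n per arm = 2(z₀.₉₇₅ + z₀.₈₀)² / h², with h = 2·arcsin√0.90 − 2·arcsin√0.60. The result is 29.8, so 30 per arm and 60 in total, which matches the stated figure.
- The unpooled formula gives 28.8, so 29 per arm and 58 in total.
- 60 × 1.10 = 66, as stated.

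The grade bounds do not enter this calculation, so correcting them leaves 66 as it is.

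**Step 5. How many patients could be ungraded, under an assumption.** Suppose that the planning rates come from this grading. With 30 per arm, the planned failures are 30 × (1 − 0.90) = 3 in the test group and 30 × (1 − 0.60) = 12 in the control group.

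| Assumed meaning of success | Ungraded, test | Ungraded, control |
|---|---|---|
| index ≥ 30% | about 3 of 30 | about 12 of 30 |
| index ≥ 70% | 0 to 3 of 30 | 0 to 12 of 30 |

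In the second row the 3 and 12 are everyone below 70%. Those below 30% are an unknown part of them.

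**The case against.** The strongest reply is that this is a slip in one bound. The words of grade 4 deny improvement, the other three bands leave only one free range, and a sensible analyst would grade below 30% as ineffective. The outcome is secondary, and the primary outcomes (5-HT, substance P, IBS-SSS) do not use the grades. All of this stands, and it limits the weight of the point. It does not remove it: the bound is stated in full in the operative definition of an analysed outcome, and nothing elsewhere in the document corrects it.

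A reader might infer more, and the document does not support it:

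- **That the sample size rests on a broken grading.** Sample size never refers to these grades. The grading is the only responder-type outcome described, so the link is plausible, but it remains an inference. The stated total also reproduces without it.
- **That about 15 of 60 patients (3 + 12), four times as many in control as in test, will drop out of the table.** That takes one assumed meaning of success and assumes that the misprint is applied literally. Under a 70% cut-off the numbers could be anything from zero up to those figures.
- **That the grade settles who is followed up.** The section on the grades says so, but the abstract describes follow-up in both groups without that limit.
- **That the article is at fault for not naming the score or the success levels.** A condensed article may leave these to the full protocol, and the section points to a guideline that is not shown here.
- **That the score must be the IBS-SSS total.** The section on that scale gives two different formulas for the total, one with two components and one with a longer, partly repeated list. It is not a safe default.

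**Conclusion.** The point holds for the grade bounds. As printed, the grades are neither exclusive nor exhaustive: every index from 30% to below 95% falls in two grades, every index below 30% falls in none, and only 95% and above is graded once. Four grades are announced and three named. The chi-square table cannot be built from this text, and the healed-and-effective set is ambiguous. This part rests on no assumption.

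The effect in patients is not fixed by the document. The range of 0 to 3 of 30 in the test group and 0 to 12 of 30 in the control group holds only if the 90 and 60 are percentages taken from this grading with a success cut-off of 30% or 70%. The upper ends apply if success means an index of 30% or more. Neither the sample size nor the primary outcomes are affected. This is a clear error in a secondary outcome that is easily put right and should be corrected before patients are graded and compared by group.

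**What to change.** Revise the paragraph under Evaluation of the evidence efficacy:

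- Define grade 4 (ineffective) as an index below 30%, negative values included.
- Give grade 3 a label and a description of its own, distinct from grade 2, and name all four grades in the opening sentence.
- Reconcile the restriction of follow-up to healed and effective cases with the abstract's follow-up of both groups, so that one statement holds throughout.

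While the paragraph is open, two clarifications would help. If the 90 and 60 in Sample size come from this grading, say which grades count as success. Name the score that actually enters the index. The formula counts a fall as improvement, whereas Bristol points rise as stools move away from the constipated types, so the choice matters. The sponsor should state the score in use rather than adopt the IBS-SSS total by default.

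The cost is one corrected paragraph and a matching line on follow-up. The grade correction needs no new data and no change to the sample size.

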**Methods/design:**

This is a randomized controlled trial. Eligible patients with irritable bowel syndrome (IBS-C) wererandomized 1:1 to a test group (massage plus probiotics) and a control group (probiotics). Patients in the test group weretreated once every 10 days for three consecutive courses of treatment (i.e., three months) and weregiven Bifidobacterium trifolium capsules 630 mg/dose three times daily 30 min after meals every day during the treatment period, with follow-up observations at the end of the third and sixth months of the treatment period. The control group weregiven Bifidobacterium trifolium capsules 630 mg/dose, 3 times a day for 3 months, with follow-up observations at the end of the third and sixth months of the treatment period. The primary outcome indicators are the concentrations of 5-HT and substance P and the IBS Severity Scale (IBS-SSS) assessment. Secondary outcomes are the Bristol Rating Scale (BRSA) score, the IBS Quality of Life Questionnaire (IBS-QOL scale) score, and the assessment of the effectiveness of the evidence. The results wereassessed at the pretreatment, posttreatment, and follow-up stages. Any side effects weresubject to assessment.

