
## Methods

### Objective

The overall objective of the study is the evaluation of the clinical rationality of the one-finger meditation massage of the abdomen for treating patients with irritable bowel syndrome (IBS-C), providing a basis for clinical promotion, to have better long-term efficacy compared with drug treatment alone, to take advantage of its painlessness and higher patient compliance, and to provide an exact and effective treatment for IBS-C in Chinese medicine.

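### The follow-up rule covers only end-of-treatment responders and stops after relapse, in conflict with the abstract; if applied, comparisons among those followed are not randomised

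*Protocol article*

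**What the plan says.** The follow-up paragraph under Evaluation of the evidence efficacy sets three conditions:

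- Who is followed: "Follow-up and observation of all healed and effective cases".
- When: "Follow-up and re-evaluation every 3 months for a total of 2 times".
- When it ends: "Symptom re-evaluation with a score ≥ 1 level is determined as a relapse, and the follow-up will be stopped next time".

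The abstract (Methods/design) describes each arm "with follow-up observations at the end of the third and sixth months of the treatment period", with no restriction to responders, and says that results are assessed before treatment, after treatment and at follow-up. The Objective includes the aim "to have better long-term efficacy compared with drug treatment alone". Statistical analysis gives independent-sample tests between groups and chi-square tests for the efficacy grading. It does not say how patients who are not followed enter a long-term comparison.

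**The concern.** Response at the end of treatment is affected by treatment. If it decides who is followed, the two followed groups are no longer the groups that randomisation formed. The control responders are the more strongly selected, because fewer controls are expected to respond. Stopping after a first relapse then removes the second-visit data of the patients who did worst. This bears on the long-term part of the objective, and no analysis plan can recover assessments that were never made.

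Two wording problems make the rule harder to apply. The relapse criterion gives no reference level. The abstract places the sixth-month observation within a treatment period that lasts three months.

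**Working it through.** **Inputs.** Sample size states "The efficiency of the test group in the preexperimental observation is 90, and the efficiency of the control group is 60" and "setting the test criterion as a = 0.05 (bilateral) and test efficacy as β = 0.20", 1:1 allocation, about 60 patients, and 66 after adding 10%. I read 90 and 60 as percentages.

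**The plan's own figure.** Arcsine formula: n per arm = 2(1.960 + 0.842)² / h², with h = 2·arcsin√0.90 − 2·arcsin√0.60 = 0.726. This gives 29.8, so 30 per arm and 60 in total. Then 60 × 1.10 = 66. The stated size reproduces, and the point here does not depend on it.

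**Who would be followed at the planning rates**, assuming that the 90/60 rates describe the same responders whom the rule follows:

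| | Test | Control | Total |
|---|---|---|---|
| Randomised | 33 | 33 | 66 |
| Followed | 33 × 0.90 = 29.7 | 33 × 0.60 = 19.8 | 49.5 |
| Not followed | 3.3 | 13.2 | 16.5 (25%) |

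With 30 evaluable per arm the followed numbers are 27 and 18.

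**Relapse among those followed (assumed figures).** Suppose 60% of patients respond in either arm and relapse at 20%. A further 30% respond only with massage and relapse at between 20% and 50%. The remaining 10% never respond.

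- Relapse among those followed, test: (0.60 × 0.20 + 0.30 × 0.20)/0.90 = 20%, up to (0.60 × 0.20 + 0.30 × 0.50)/0.90 = 30%. Control: 20%.
- Sustained response among all randomised, test: 0.90 × 0.80 = 72%, down to 0.90 × 0.70 = 63%. Control: 0.60 × 0.80 = 48%.

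The same patients make massage look equal or worse on relapse among those followed, and clearly better on sustained response among all randomised.

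**Mean index among those followed (assumed normal, SD 30, effect fully persisting).** Means that give 90% and 60% at an index of 30 or more are 30 + 1.282 × 30 = 68.4 and 30 + 0.253 × 30 = 37.6, a difference of 30.8.

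- Followed if the index is at least 30: the means become 74.3 and 56.9, a difference of 17.4.
- Followed if the index is at least 70: 48% and 14% are followed, and the difference is 8.1. Not followed: 33 × 0.52 + 33 × 0.86 = 17.2 + 28.4, about 45 of 66.

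This model shows direction only. The index is (pre − post)/pre, which cannot exceed 100% for non-negative scores, yet the model puts about 15% of test patients above 100. The SD is not from the document. The 70% case also assumes that 90/60 refers to the 30% cut, which Sample size does not say. If 90/60 referred to the 70% cut, the same model would again give 90% and 60% followed and a difference of 17.4.

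**The case against.** The strongest reply is about scope. The rule stands under one secondary outcome, the efficacy grading, and no sentence applies it to IBS-SSS, Bristol or IBS-QOL. The abstract has both arms followed without restriction, and the schedule figure, which might settle the matter, is not shown in the text available. A reader might infer that the long-term comparison will certainly be made in outcome-selected subsets. The document does not support that: it contradicts itself on who is followed, and it names no specific follow-up analysis. What remains is that this paragraph is the only operational follow-up rule in the text and is worded generally.

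The second reply is that a sustained-response endpoint survives the rule. Non-responders and relapsers are failures by definition, so status is known for everyone apart from ordinary loss. This is correct. The bias arises for scale scores, or for relapse, compared among those followed. However, the protocol does not name sustained response as its long-term endpoint, and the abstract does describe assessment of results at follow-up.

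A third possible inference is that every effective but uncured patient would count as relapsed at the first visit. The criterion may equally mean worsening by one level. The text is unclear and does not establish the extreme reading.

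Leaving detail to a fuller document is no answer here, because the article states a rule.

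**Conclusion.** The point holds as a contradiction with a consequence. If the responder-only rule is followed, about 10% of the test arm and 40% of the control arm leave follow-up because of their outcome: about 3 and 13 patients at the planning rates, and more if effective requires an index of 70% or more. The grading is itself garbled: four levels are announced but three are named, the 30–70% level has no name, and the range given for ineffective overlaps others. The size of the followed subset therefore cannot be fixed from the text.

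Comparisons of scale scores or relapse within that subset would not be protected by randomisation. The shrinkage from 30.8 to 17.4 or 8.1 points is an illustration under an ill-fitting model and should not be read as a forecast. Nor does the point reach the end-of-treatment comparisons. Serum 5-HT and SP are measured only before and after treatment, and nothing shows the response rates behind the sample size to depend on follow-up.

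**What to change.** Reconcile the abstract with the follow-up paragraph so that all 66 randomised patients are assessed on IBS-SSS, Bristol and IBS-QOL at both follow-up visits, whatever their response and also after relapse. Base the long-term comparison on all randomised patients, for example on sustained response with non-responders and relapsers counted as failures, together with the scale scores. Relapse among responders can still be reported descriptively. State the reference level against which relapse is judged, and reconcile the abstract's timing of follow-up with the three-month treatment.

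The cost is about 16 to 17 more patients to contact per visit at the planning rates, or about 45 of 66 under the 70% reading and the illustrative model, plus relapsed patients at the second visit. Telephone contact is already permitted, the inclusion criteria already require that patients can receive follow-up, and the change concerns assessment only, not treatment.

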#### Statistical methods

##### Sample size

The test group sample size (massage with the probiotics group) and the control group (probiotics group) were randomly grouped in a 1:1 ratio, and the sample size was determined according to the bilateral hypothesis test, setting the test criterion as a = 0.05 (bilateral) and test efficacy as β = 0.20. The efficiency of the test group in the preexperimental observation is 90, and the efficiency of the control group is 60. The required sample was calculated to be approximately 60 cases, with an increase of 10% of cases taken off, and the actual sample size is approximately 66 cases; that is, 33 cases in the test group and 33 cases in the control group are selected.

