### Outcome measures

#### Primary outcome

##### 5-HT and SP concentration

Serum 5-HT and SP concentrations in patients were determined before and after treatment using an enzyme-linked immunosorbent assay (ELISA). The level of 5-HT is closely related to the presence of diarrhea or constipation in irritable bowel syndrome, as well as SP [55, 56]. We will compare the efficacy of the two groups by ELISA of serum 5-HT and SP in patients before and after treatment.

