##### IBS Severity Scale (IBS-SSS) assessment

Outcomes included the level of abdominal pain, frequency of abdominal pain, level of bloating, bowel satisfaction and effects on life. (1) Abdominal pain severity, frequency of pain in the abdomen, abdominal distension degree, defecation satisfaction, and effects on life were included. (2) Abdominal pain frequency score: abdominal pain frequency score = actual abdominal pain days/14 × 100. (3) IBS-SSS scale total score: IBS-SSS scale total score = abdominal pain severity score + abdominal pain frequency score. IBS-SSS scale total score = abdominal pain score + abdominal pain frequency score + abdominal distension score + bowel satisfaction score + impact on life satisfaction score + impact on life score.

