### Statistical analysis

Two independent researchers will record all experimental data on CRF forms and enter them into the computer. Data will counted by statisticians using SPSS 19.0 statistical software. The mean ± standard deviation (M ± SD) will used for measurement data, paired sample tests will be used for before-and-after control within groups, independent sample tests will used for comparisons between groups, and chi-square tests will be used for efficacy grading. p < 0.05 is considered a statistically significant difference.

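### Three continuous primary outcomes share one flat p<0.05 rule, and the sample size is for a response rate, so the error rate across the primaries is uncontrolled and the stated 80% power belongs to none of them

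*Protocol article*

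**What the plan says.** The abstract of the protocol article lists three primaries: "The primary outcome indicators are the concentrations of 5-HT and substance P and the IBS Severity Scale (IBS-SSS) assessment". The Primary outcome section repeats all three. Two are laboratory concentrations: "Serum 5-HT and SP concentrations in patients were determined before and after treatment using an enzyme-linked immunosorbent assay (ELISA". The third is a sum score: "IBS-SSS scale total score = abdominal pain score + abdominal pain frequency score + abdominal distension score + bowel satisfaction score", and so on through its components.

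The secondary outcomes in the abstract are the Bristol score, IBS-QOL "and the assessment of the effectiveness of the evidence". The section on evidence efficacy defines that last one as a percentage reduction in a score it does not name: "the efficacy index was calculated using the nimodipine method". The reduction is then cut into grades.

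Under Sample size the design values are given as "setting the test criterion as a = 0.05 (bilateral) and test efficacy as β = 0.20", followed by the effect assumption: "The efficiency of the test group in the preexperimental observation is 90, and the efficiency of the control group is 60". This leads to about 60 patients, and to 66 (33 per arm) after adding 10%.

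Under Statistical analysis, measurement data are summarised as mean and SD and compared between groups by independent-sample tests. Efficacy grades are compared by chi-square. The only decision rule is that p below "0.05 is considered a statistically significant difference".

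**The concern.** Two parts of the plan do not fit the primary outcomes.

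First, with three primaries and one unadjusted threshold, nothing says whether one significant result is enough or all three are needed. As written, a shift in one serum marker with no symptom benefit could be reported as a positive primary result, at an overall error rate above the 5% that a reader would assume.

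Second, the effect assumption is a pair of rates, while every primary is continuous and compared by means. No mean difference or SD is given for any of them. A reader will naturally take the 80% power as covering the primaries, and the calculation does not support that.

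**Working it through.** **Inputs from the protocol article.** Three primaries (abstract; Primary outcome). Two-sided alpha 0.05, beta 0.20, 90 against 60, 1:1 allocation, 60 patients before and 66 after the dropout allowance (Sample size). Threshold 0.05 and independent-sample tests (Statistical analysis). The correlations, and the power model for continuous outcomes, are assumptions made for this check.

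**1. Reproducing the stated 60.** Read 90 and 60 as percentages. Then (1.960 + 0.842)² = 7.849.

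- Arcsine formula: 7.849 / [2 × (arcsin√0.9 − arcsin√0.6)²] = 7.849 / [2 × (1.2490 − 0.8861)²] = 29.8, so 30 per arm and 60 in total, an exact match.
- Unpooled normal formula: 7.849 × (0.9×0.1 + 0.6×0.4) / 0.3² = 7.849 × 0.33 / 0.09 = 28.8, so 29 per arm and 58 in total.
- Pooled-variance formula: 31.5, so 32 per arm and 64 in total. With continuity correction: 38 per arm and 76 in total.
- Exact enumeration of the uncorrected chi-square test at 30 per arm: power 79.6%.
- Dropout: 60 × 1.10 = 66, as stated.

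The arithmetic stands, and it is a two-proportion calculation. The outcome it best fits is the graded efficacy index, which is secondary and is tested by chi-square.

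**2. Error rate across three primaries.** Suppose there is no true effect on any of the three, and significance on any one counts as success.

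- Independent tests, either direction: 1 − 0.95³ = 14.3%.
- Independent tests, errors favouring massage only: 1 − 0.975³ = 7.3%.
- Equally correlated tests (simulation, 2,000,000 draws):

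| Assumed correlation | Either direction | Favouring massage only |
|---|---|---|
| 0.3 | 13.6% | 6.8% |
| 0.5 | 12.5% | 6.3% |
| 0.7 | 10.9% | 5.5% |
| 0.9 | 8.3% | 4.2% |

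The reference values for a single test at two-sided 0.05 are 5% and 2.5%.

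**3. What 30 evaluable per arm gives on a continuous primary.** For a two-sample t-test with 58 degrees of freedom, the noncentrality is d × √(30/2), where d is the standardised difference. Solving for 80% power:

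- alpha 0.05: d = 0.74
- alpha 0.05/3 = 0.0167: d = 0.86

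The normal approximation √(2/30) × (z for alpha + 0.842) gives 0.72 and 0.84, which is close. The protocol article states no d for any primary, so the power that applies to them cannot be computed from it.

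**The case against.** Several objections have force.

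- **The error rate is conditional.** A reader might infer that the trial has a 14% chance of a false primary success. The documents do not support that as a flat statement. No success rule is given; 14.3% needs independence, an any-one-of-three rule and errors counted in both directions. If all three had to be significant, the error rate would not inflate, and the cost would fall on joint power instead. This stands, and the figure must carry its assumptions.
- **Multiplicity rules are often left to the SAP.** True in general, and the SAP is not shown. But the article fixes a flat threshold alongside three primaries and a complete sample-size calculation. A SAP could add multiplicity control; it could not turn a response-rate calculation into one for continuous outcomes. This stands only in part.
- **The endpoint behind the 90 and 60 is not named.** Tying them to the secondary efficacy grade is a strong inference, not a stated fact. The score inside the efficacy index is unnamed and could be IBS-SSS. Even then, a dichotomised IBS-SSS is not the continuous primary that is tested.
- **The trial may not be underpowered.** A reader might infer that it is. The documents do not show this. If the 90% and 60% came from dichotomising a symptom score that is normal with equal variance in both arms, the implied difference would be 1.28 − 0.25 = 1.03 SD. At 30 per arm that gives about 97% power at 0.05 and 93% at 0.0167. This too is an assumption, and it says nothing about 5-HT or SP. What is established is narrower: no effect size is stated for any primary.
- **Demoting the biomarkers is not an obvious remedy.** The Background makes showing regulation of 5-HT and SP a stated aim, and the IBS-SSS section gives two different formulas for the total. This stands, and it is why the fix below leads with Holm.

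**Conclusion.** The point holds in a limited form. Three continuous outcomes are primary under one flat 0.05 threshold. If significance on any one is read as primary success, the familywise two-sided error is 14.3% under independence and about 8% to 14% for assumed correlations of 0.9 to 0, or about 4% to 7% in favour of massage.

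The 60 patients are correctly derived, but for 90% against 60% response, most likely the secondary efficacy grade. The stated 80% power therefore does not apply to the primaries as tested. The documents do not show that power on the primaries is too low; they give no basis for stating it. The structural mismatch is certain. The size of the error inflation depends on the success rule and the correlations, neither of which is stated.

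**What to change.** 1. **Statistical analysis.** Keep the three primaries and test their between-group comparisons at the end of treatment by Holm at an overall two-sided 0.05: the smallest p-value against 0.05/3 = 0.0167, the next against 0.025, the largest against 0.05, stopping at the first that fails.
2. **Alternative, if the investigators prefer it.** Declare one primary before any unblinded outcome is seen. If it is IBS-SSS, first reconcile the two formulas for its total: one adds two components, the other is a longer sum.
3. **Sample size.** Name the endpoint behind the 90 and 60, and state that the 80% power is for that response rate. Add that 30 evaluable per arm gives 80% power on a continuous primary for a standardised difference of 0.74 at alpha 0.05 and 0.86 at 0.05/3, and that no effect size was assumed for any primary.

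Enrolment is unchanged. The costs are a stricter initial threshold for each primary, a less favourable power statement, and a protocol and registry amendment. The Trial design section already describes the 66 participants as randomised, although tenses are mixed throughout, so the amendment should be dated and should state that unblinded outcomes had not been seen.
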